## Abstract

**Background:**

Anthracycline-induced cardiotoxicity is a major factor affecting the long-term prognosis of cancer patients. Atrial arrhythmias, as common manifestations of cardiotoxicity, significantly impair quality of life and may compromise the effectiveness of anticancer therapy, representing a significant clinical challenge. Wenxin Keli (WXKL), a traditional Chinese medicine formulation with the effects of replenishing qi, nourishing yin, and promoting blood circulation, has demonstrated potential anti-arrhythmic benefits. However, high-quality evidence supporting its application in the field of cardio-oncology remains limited. This study aims to systematically evaluate the efficacy and safety of WXKL in patients with anthracycline-induced atrial arrhythmias.

**Methods:**

This is a multicenter, randomized, double-blind, placebo-controlled clinical trial. A total of 152 eligible participants will be enrolled and randomly assigned to receive either WXKL or placebo for 3 months, followed by a 3-month follow-up period. The primary outcome is the proportion of patients free from atrial arrhythmias at 3 months, defined as the absence of atrial fibrillation (AF) episodes lasting ≥30 s or premature atrial contractions (PACs) ≥100 beats per 24 h on Holter monitoring. Secondary outcomes include AF burden, PACs count, echocardiographic parameters, cardiac biomarkers (cTnI and NT-proBNP), quality of life (FACT-G), functional status (ECOG), clinical symptom scores, and anxiety scores (SAS) at 3 and 6 months, as well as safety assessments.

**Discussion:**

This study is designed to provide high-level clinical evidence for the use of WXKL in the treatment of anthracycline-induced atrial arrhythmias. By incorporating both PACs and AF as a composite endpoint, the study aims to more comprehensively capture the overall burden and dynamic progression of atrial arrhythmias, and to inform cardio-protective strategies during cancer therapy.

**Trial registration:**
http://itmctr.ccebtcm.org.cn/zh-CN, International Traditional Medicine Clinical Trial Registry Platform, ITMCTR2025000704.

## Introduction

Anthracycline has become cornerstone drug in the treatment of malignant tumors such as breast cancer, lymphoma, and leukemia due to their potent antitumor activity. Even amid the rapid advancement of immunotherapy and targeted therapies, their clinical role remains irreplaceable (1). However, the non-specific distribution characteristics of anthracycline result in significant cardiotoxicity alongside its antitumor effects, with this risk increasing as cumulative drug dose. Elderly patients, due to age-related decline in physiological function, exhibit a much higher incidence of cardiotoxicity compared to younger individuals (2–4). This anthracycline-induced cardiotoxicity (AIC) has long posed a significant challenge in clinical practice—not only severely limiting the clinical application of anthracycline but also profoundly impacting patient prognosis and quality of life. It represents a core challenge that must be overcome in the clinical use of anthracycline (5, 6). Clinically, AIC manifests in acute and chronic forms: Acute toxicity typically occurs within two weeks after a single dose or single course, primarily presenting as electrocardiographic (ECG) abnormalities and atrial or ventricular arrhythmias (7); chronic cardiotoxicity may develop months to years after treatment cessation, primarily manifesting as cardiomyopathy and heart failure (8). Research indicates that AIC is characterized by irreversible cardiac damage and myocardial cell death, with mechanisms involving: 1) oxidative stress and excessive ROS production; 2) topoisomerase II inhibition and DNA double-strand breaks leading to abnormal gene transcription and apoptosis; 3) activation of the apoptosis pathway due to mitochondrial dysfunction (6, 9). Arrhythmias, particularly atrial arrhythmias, are a major clinical manifestation of AIC that are intimately linked to the use of anthracycline. Data indicate that the overall risk of arrhythmias in patients receiving anthracycline-based chemotherapy increases to 90%, with the risk of atrial arrhythmias rising to 114% (3, 10). As a typical atrial arrhythmia, atrial fibrillation (AF) has a prevalence of up to 10.3% in this population, and the risk further increases with cumulative anthracycline dose (11). In addition to AF, premature atrial contractions (PACs) are also a common form of atrial arrhythmia in clinical practice. Previous studies have shown that frequent PACs not only reflect a state of atrial electrophysiological instability but also serve as an important precursor and predictive marker of AF, with their frequency positively correlated with the subsequent risk of AF (12, 13). Therefore, PACs and AF share a pathophysiological continuum and progressive relationship, jointly reflecting different stages of atrial electrical remodeling. For cancer patients, atrial arrhythmias exert multidimensional effects. They cause symptoms such as palpitations, chest tightness, and dizziness, diminishing quality of life. They also elevate the risk of stroke, heart failure, and mortality. Importantly, severe arrhythmias may necessitate interruption of chemotherapy, directly compromising anticancer efficacy (14). Consequently, Therefore, the effective identification and management of atrial arrhythmias induced by anthracycline drug are of great importance for ensuring the smooth implementation of anticancer therapy and improving patient prognosis (4, 15).

Nevertheless, current clinical management of anthracycline-induced atrial arrhythmias faces significant limitations. Conventional anti-arrhythmic drugs can provide some benefit, but they lack optimized regimens tailored to the unique physiological state of cancer patients—such as interactions with chemotherapeutic agents and multi-organ functional impacts. Additionally, certain drugs present issues like poor tolerability and pronounced side effects. Concurrently, traditional Chinese medicine (TCM) has gained increasing attention in the field of cardio-protection for cancer patients. Among these, Wenxin Keli (WXKL) holds particular promise. As the first Chinese patented anti-arrhythmic herbal formulation approved by the China Food and Drug Administration (16). WXKL is composed of five herbal ingredients: Codonopsis pilosula, Panax notoginseng, Polygonatum sibiricum, Nardostachys jatamansi, and Amber, which has the effects of replenishing qi, nourishing yin, and promoting blood circulation, and is widely employed in clinical practice for treating various arrhythmias (17). Mechanistic studies have confirmed that WXKL exerts its therapeutic effects through multiple pathways, including improving cardiomyocyte electrophysiology, counteracting oxidative stress, and regulating calcium homeostasis, demonstrating efficacy in AF and ventricular premature beats (18, 19). Furthermore, the agent exhibits a favorable safety profile and good tolerability with long-term use, underscoring its clinical utility (20). Although existing studies have preliminarily explored the the anti-arrhythmic mechanisms of WXKL, most are small-sample, single-center designs. In the field of cardio-oncology, no high-quality randomized controlled trials have yet validated its efficacy and safety for treating anthracycline-induced atrial arrhythmias, resulting in a lack of evidence-based support for its clinical application. Based on this, this study aims to conduct a multicenter, randomized, double-blind, placebo-controlled clinical trial to systematically evaluate the efficacy of WXKL in treating anthracycline-induced atrial arrhythmias. This study will not only fill the evidence-based gap in the field of onco-cardiology regarding the integrated traditional Chinese and Western medicine treatment of related complications, but also provide clinicians with a new cardio-protective strategy that combines efficacy and safety. It holds significant clinical importance for optimizing treatment regimens for patients undergoing anthracycline chemotherapy and enhancing the overall efficacy of comprehensive cancer therapy.

## Methods

### Study design and setting

This trial is a multicenter, double-blind, placebo-controlled study with two parallel groups designed to evaluate the efficacy of WXKL.The protocol was formulated in accordance with the SPIRIT statement and the Declaration of Helsinki (2013 Revision), as well as the Guidelines for Good Clinical Practice (GCP). The start and end of recruitment had been planned to be December 2025 and March 2028, respectively.

Before the experiment begins, researchers will conduct a training program to ensure that all participating medical staff fully understand each part of the trial. The trial will be conducted at multiple clinical centers in China, including Guang'anmen Hospital of the China Academy of Chinese Medical Sciences, Qilu Hospital of Shandong University, Xingtai People's Hospital, Affiliated Hospital of North China University of Science and Technology, Jinqiu Hospital of Liaoning Province, Tianjin Medical University Cancer Institute&Hospital, and Dezhou Second People's Hospital. After confirming eligibility and signing the informed consent form, 152 subjects receiving anthracycline treatment will be randomly allocated to either the WXKL or placebo groups in a 1:1 ratio. The study is divided into four phases: recruitment, allocation, intervention, and completion. Each participant will only be enrolled once. In addition to anthracycline chemotherapy and conventional anti-arrhythmic medications, participants will receive either WXKL or placebo treatment. During the study period, each participant will undergo three visits: baseline (Visit 1), month three (Visit 2), and month six (Visit 3). In Phase 1, participants are recruited from the oncology department, where they will undergo a physical examination and eligibility assessment. Those who match the inclusion criteria will receive a three-month pharmacological intervention. In Phase 2, following the completion of the intervention, participants will undergo clinical efficacy and safety assessments. Phase 3 is the follow-up period, during which participants will be followed up at the sixth month to gather their metrics again and assess clinical efficacy. The participant flowchart is shown in Figure 1, and the study schedule is shown in Table 1.

**Figure 1 F1:**
[figure not shown]
The participant flowchart. WXKL, Wenxin Keli; ECHO, echocardiography; cTnI, cardiac troponin I; NT-pro-BNP, N-terminal pro-B-type natriuretic peptide; FACT-G, functional assessment of cancer therapy for general. SAS, self-rating anxiety scale.

**Table 1 T1:** Schedule of enrollment, intervention and assessment.

Study procedure		Intervention		
		Visit 1	Visit2	Visit3
Time point		baseline	month 3	month 6
Evaluation of inclusion/exclusion criteria		●		
Informed consent		●		
Basic information and demographics		●		
Past, personal and family history		●		
Cancer typing and staging		●		
Previous cancer treatment history		●		
Scale score	ECOG score	●	●	●
	Clinical symptom score	●	●	●
	FACT-G	●	●	●
	SAS	●	●	●
Complementary check-up	24 h Holter	●	●	●
	ECHO	●	●	●
	Complete blood count	●	●	●
	Liver function tests	●	●	●
	Renal function tests	●	●	●
	Electrolyte examination	●	●	●
	NT-pro-BNP	●	●	●
	cTnI	●	●	●
Merge Medication Records		●	●	●
Adverse Event and Significant Incident records			●	●
Test Reliability Evaluation		●		
Evaluation of Therapeutic Efficacy			●	●
Clinical Trial Summary Form				●
Summary Table (Test Report Attachment Area)		●	●	●

According to SPIRIT 2013 Statement: Defining Standard Protocol Items for Clinical Trials.

The study protocol has been approved by the Medical Ethics Committee of Guang'anmen Hospital, Chinese Academy of Medical Sciences, China (NO. 2024-194-KY-02) and registered on the International Traditional Medicine Clinical Trial Registry Platform (No. ITMCTR2025000704). All participants will provide written informed permission before any study-related operations are conducted. During the trial, any modifications to the study design will be promptly reported to the Ethics Committee.

### Participation and recruitment

#### Recruitment and consent

Potential participants will be initially identified via the hospital's electronic medical record system and routine outpatient visits. Clinical staff will approach individuals who meet the basic diagnostic criteria and invite them to join the study. Interested candidates will then undergo comprehensive screening, including detailed evaluations to confirm whether they satisfy the predefined inclusion and exclusion criteria. Once eligibility is confirmed, participants will receive complete study information and provide informed consent, thereby ensuring their voluntary involvement in the trial.

#### Inclusion criteria

The inclusion criteria for this study include the following conditions: 1) Age 18–80 years; 2) Having a confirmed pathological type, receiving chemotherapy for the first time, with an expected cumulative anthracycline dose ≥200 mg/m², and PAVs or AF after at least one cycle of anthracycline therapy, with ambulatory electrocardiography showing PAVs ≥100 beats per 24 h or meeting the diagnostic criteria for AF; 3) No history of PAVs or AF; 4) No prior history of chest radiotherapy, targeted therapy, or immunotherapy; 5) Eastern Cooperative Oncology Group (ECOG) performance status < 2; 6) Willing to be randomly assigned to either the WXKL group or the control group; 7) Voluntary participation in the trial and provision of signed informed consent.

#### Exclusion criteria

The exclusion criteria for this study include the following:1) Patients with inadequately controlled heart failure (left ventricular ejection fraction <50%); 2) Patients with QTc > 500 ms, a history of QTc prolongation (congenital or acquired), or severe bradyarrhythmia; 3) Patients who have experienced new-onset major vascular events within the past 3 months, such as myocardial infarction or cerebral infarction; 4) Patients with diagnosed cardiomyopathy (ischemic, dilated, restrictive, or hypertrophic) or moderate to severe valvular heart disease; 5) Patients with inadequately controlled blood pressure: systolic blood pressure ≥180 mmHg or diastolic blood pressure ≥ 110 mmHg, or systolic blood pressure <90 mmHg or diastolic blood pressure <60 mmHg; 6) Patients with chronic kidney disease and an estimated glomerular filtration rate (eGFR) <30 mL/min/1.73 m²; 7) Patients with serum potassium >5.5 mmol/L; 8) Patients with alanine aminotransferase (ALT) or aspartate aminotransferase (AST) levels exceeding three times the upper limit of normal; 9) Pregnant or lactating women; 10) Patients with allergies to or contraindications for the study drug components; 11) Patients currently participating in other clinical trials.

### Sample size calculation

To our knowledge, this is the first clinical trial to evaluate a TCM formulation for the treatment of anthracycline-induced atrial arrhythmias. Currently, no published data are specifically available for atrial arrhythmias induced by anthracycline. Therefore, the sample size estimation was based on existing studies of TCM in the treatment of AF or PVCs, together with clinical experience and expert consensus (21–23). We assumed that the proportion of patients free from atrial arrhythmias would be 29% in the WXKL group and 10% in the placebo group. Based on a two-sided significance level of 0.05 and a statistical power of 80%, the required sample size was calculated using PASS version 15. The calculation indicated that 68 participants were needed per group. Considering an anticipated dropout rate of 10% and rounding to whole numbers, the final sample size was set at 76 participants per group, resulting in a total of 152 participants to be enrolled in this trial.

### Randomization and blinding

This study will use centralized randomization. An independent statistical center will generate the randomization sequence. participants will be allocated in a 1:1 ratio to guarantee uniformity of baseline characteristics, and each participant will be assigned a trial code for identification. The randomization sequence details have been uploaded to the central randomization system. The trial is double-blinded for both investigators and participants. All trial medications—WXKL for the intervention group and placebo for the control group—are produced, packaged, and labeled by Shandong Buchang Pharmaceutical Co., Ltd. (Shandong, China). The placebo matches WXKL in appearance, texture, and weight. All packages are identical in outward form to maintain blinding throughout the study. In the event of a serious adverse event, the investigator may perform emergency unblinding for the affected participant and report accordingly to the ethics committee. After trial completion, statisticians will conduct the first unblinding and perform statistical analysis based on the grouped data. Following analysis, a second unblinding will reveal the final group allocations. All data collection and outcome assessments will be carried out by third-party personnel not involved in trial design or participant recruitment.

### Intervention measures

Participants will be randomly assigned to either the intervention group or the control group and will receive treatment for 3 months. During the study period, the use of any other traditional Chinese medicines with similar components to WXKL will be prohibited. From Day 1 after enrollment, participants in the intervention group will receive WXKL (National Drug Approval Number Z10950026), while those in the control group will receive a matched placebo. Both treatments will be administered orally as granules dissolved in warm water, one sachet (5 g) three times daily. Drug dispensing will be managed by designated personnel, with careful counting and documentation to ensure accurate allocation according to the randomization code. At the end of the trial, all unused medications will be collected and destroyed by designated staff.

Concomitant medications: (a) All participants will receive anthracycline-based chemotherapy according to standardized regimens prescribed by their treating physicians (24, 25). (b) According to current clinical guidelines, *β*-blockers are recommended as first-line agents for ventricular rate control in atrial arrhythmias. Therefore, for patients with symptoms or clinical indications, *β*-blockers will be administered as background antiarrhythmic therapy. The initiation, dose titration, and anticoagulation strategies will be determined based on patients' clinical status and relevant guidelines (26), to ensure both safety and consistency across study centers. (c) Concomitant use of medications for other comorbid conditions will be permitted. However, the use of other anti-arrhythmic drugs (except *β*-blockers) will be prohibited to minimize potential confounding effects. In addition, the use of cardio-protective agents specifically targeting anthracycline-induced cardiotoxicity, such as dexrazoxane, will not be allowed. All concomitant medications during the study will be recorded in detail in the case report forms (CRF).

Assigned interventions may be discontinued or modified in cases of serious adverse events, participant withdrawal, or clinical deterioration. Any such changes will be fully documented and submitted to the ethics committee for review.

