### Statistical analysis

All statistical analyses will be performed using SPSS (version 26.0, IBM) and R (version 4.1.1). All tests will be two-sided, and a *P* value <0.05 will be considered statistically significant. The primary analysis will follow the intention-to-treat (ITT) principle, including all randomized participants and analyzing them according to their assigned groups. A per-protocol (PP) analysis will be conducted as a sensitivity analysis, and the safety analysis will include all participants who received at least one intervention. Baseline characteristics will be described by group. Continuous variables will be presented as mean ± standard deviation or median (interquartile range), depending on their distribution, while categorical variables will be expressed as frequencies and percentages. All analyses will be reported in accordance with the CONSORT Statement.

The primary outcome is the proportion of patients free from atrial arrhythmias at 3 months after intervention, which is a binary variable. It will be analyzed using a generalized linear model (GLM) with a binomial distribution and a log link function. Treatment group and study center will be included as fixed effects, and pre-specified baseline covariates—including age, sex, cancer subtype, cumulative anthracycline dose, and medical history—will be further adjusted. Results will be presented as risk ratios (RR) with corresponding 95% confidence intervals. Secondary continuous outcomes, such as AF burden, premature PAVs counts, echocardiographic parameters, and relevant biomarkers, will be analyzed using linear models (LM), with adjustment for baseline values. For repeated measures data (e.g., baseline, 3 months, and 6 months), mixed-effects models will be applied to evaluate treatment effects over time.

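### β-blockers are the one anti-arrhythmic class allowed alongside study drug, yet neither the described randomisation nor the primary model uses β-blocker status: the cost is precision and possible attenuation, not bias at entry

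*Protocol article*

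**What the plan says.** **Co-medication (Protocol article, Intervention measures, concomitant medications b and c).** β-blockers are given as background anti-arrhythmic treatment to patients with symptoms or a clinical indication. "The initiation, dose titration, and anticoagulation strategies will be determined based on" clinical status and the cited guidelines, with consistency across centres as a stated aim. No stable-dose requirement before randomisation and no time window afterwards is stated. All other anti-arrhythmic drugs "will be prohibited to minimize potential confounding effects".

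**Randomisation (Randomization and blinding).** Allocation is central and 1:1. No stratification factor is named.

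**Primary model (Statistical analysis).** A log-link binomial model has treatment and centre as fixed effects and adjusts for pre-specified covariates, including "age, sex, cancer subtype, cumulative anthracycline dose, and medical history". β-blocker use is not among those named. The primary analysis is intention-to-treat, with per-protocol as sensitivity analysis.

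**Data available.** Table 1 schedules "Merge Medication Records" at all three visits, and Baseline assessments lists comorbidities with their related medications.

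**The concern.** The article treats anti-arrhythmic co-medication as a confounder and then leaves the one permitted class out of the analysis that it specifies. Two separate issues follow.

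- **Use at entry.** β-blocker status is a plausible predictor of the month-3 Holter result. Leaving it out of both design and model forgoes some precision and leaves a chance imbalance unadjusted.
- **Use after randomisation.** Patients enter with newly found arrhythmia, so decisions to start a β-blocker may well fall around or after Day 1. Blinding stops prescribing driven by knowledge of the arm. It does not stop prescribing driven by persisting arrhythmia or symptoms, which an effective study drug would make rarer on active treatment. A placebo patient whose Holter is clean after a start counts as arrhythmia-free.

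Because β-blockers are permitted, a start is not a protocol deviation, so the per-protocol analysis would not isolate it. At stake is mainly how a small or null result would be read: no effect of the study drug, or extra background treatment on placebo.

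**Working it through.** **1. The plan's own sample size.** Inputs from Sample size calculation: "free from atrial arrhythmias would be 29% in the WXKL group and 10% in the placebo group"; two-sided alpha 0.05; power 80%. Pooled-variance formula without continuity correction, with mean rate (0.29 + 0.10)/2 = 0.195:

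n = [1.960 × √(2 × 0.195 × 0.805) + 0.842 × √(0.29 × 0.71 + 0.10 × 0.90)]² / 0.19² = 67.1, rounded up to 68.

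This matches "The calculation indicated that 68 participants were needed per group". With 10% dropout, 68/0.90 = 75.6, rounded up to the stated 76. Power is 80.5% at 68 per group and 84.8% if all 76 are evaluable. The calculation is sound but has little reserve.

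**2. Responders available to the model.** 76 × 0.29 + 76 × 0.10 = 22.0 + 7.6 = 29.6, about 30. The seven listed centres need 6 terms, treatment 1 and the five named covariates at least 5. That is at least 12 terms besides the intercept, or about 2.5 responders per term.

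**3. Chance imbalance at entry.** Assumption: 30% to 50% of patients use a β-blocker at randomisation (not in the document). The standard deviation of the between-arm difference is √(2p(1−p)/76), which is 0.074 at 30% and 0.081 at 50%. A difference above 10 points then occurs in about 18% to 22% of trials. If users and non-users differ by 5 to 20 points in the chance of being arrhythmia-free (assumed), a 10-point imbalance shifts the comparison by 0.10 × 5 to 0.10 × 20 = 0.5 to 2 points, in either direction. The planned difference is 19 points.

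**4. Attenuation from later use.** The document gives no uptake or effect figures, so all inputs are assumptions. Let x be the excess share of placebo patients who start or increase a β-blocker, and q their chance of being arrhythmia-free. Hold the active arm at 29%. The placebo rate is 0.10(1−x) + qx. Power is for the unadjusted two-proportion test at 68 per group.

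| q | x | Placebo rate | RR | Power |
|---|---|---|---|---|
| none | 0 | 10.0% | 2.90 | 80.5% |
| 15% | 10% | 10.5% | 2.76 | 78.0% |
| 15% | 40% | 12.0% | 2.42 | 69.4% |
| 20% | 20% | 12.0% | 2.42 | 69.4% |
| 30% | 20% | 14.0% | 2.07 | 56.8% |
| 30% | 40% | 18.0% | 1.61 | 32.6% |

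**5. How strong are these assumptions?** The plan's own effect means that the study drug converts (0.29 − 0.10)/0.90 = 21% of patients who would otherwise stay arrhythmic. On the same scale, q = 15% means (0.15 − 0.10)/0.90 = 6%, q = 20% means 11% and q = 30% means 22%. The lowest rows of the table therefore need a β-blocker about as effective as the assumed study drug, with a large excess of use on placebo.

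**The case against.** The case against is substantial, and much of it stands.

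- **Randomisation already balances entry use in expectation.** Correct. Chance imbalance is ordinary sampling variation, covered by the test and the confidence interval. A reader might infer that unbalanced β-blocker use biases the comparison; the documents do not support that.
- **Intention-to-treat answers a legitimate question.** Correct. It estimates the effect of adding the study drug to guideline care. Extra background treatment on placebo would pull the estimate towards no effect.
- **Starts at any time, with each centre deciding for itself, is not what the text says.** Correct. Open timing is inferred from the absence of a stated limit. The article names a common guideline basis and calls the treatment background, and Study design and setting describes study drug as given on top of conventional anti-arrhythmic medication. Table 1 has no Holter or visit between baseline and month 3, so the first scheduled Holter that could prompt a change is the primary one. Symptom-driven starts remain possible.
- **The effect of β-blockers on this endpoint is not documented.** Largely correct. The article justifies them by ventricular rate control, though it also calls them anti-arrhythmic. It does not say that they bring the ectopic count below 100 per 24 h. Nor does it say whether the 29% and 10% already allow for β-blocker use, so part of the loss in step 4 may be double-counted.
- **The analysis plan may hold the rest.** Tables of concomitant medication and a supplementary analysis could well be in a document that is not shown, so their absence is not itself a fault. The covariate list is different, because it is stated in this article. It is introduced as a non-exhaustive list, but β-blocker use is not named and the medical-history term is undefined.

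**Conclusion.** The point holds in limited form. The article singles out anti-arrhythmic co-medication as a confounder, permits one class of it, and uses that class in neither the described randomisation nor the named covariates of the primary model. For use at entry the loss is precision and exposure to chance imbalance, worth roughly 0.5 to 2 points under the assumptions shown. For later use, the intention-to-treat effect may be attenuated if placebo patients start or increase β-blockers more often, by an amount that the document gives no figures to estimate.

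A reader might infer that β-blocker use on placebo would hide a true effect, or might take the low power values in the table as a forecast. Neither is supported: those values depend on assumed uptake and effect, and a 10% excess with a modest effect moves power only from 80.5% to 78.0%. The sample size reproduces and the primary estimate stays valid. The change is worth making because it costs little and would help in reading a null result.

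**What to change.** 1. **At randomisation:** record β-blocker use (yes/no) in the central system and include it as a covariate in the primary model, or stratify on it. Stratification must be set before patients are randomised; recruitment was planned from December 2025, so if it has begun, the covariate is the workable option, fixed before unblinding. Let it replace the undefined medical-history term, so that a model with about 30 expected responders does not grow.
2. **In the analysis:** keep intention-to-treat (treatment policy) as primary. Report β-blocker starts and dose increases after randomisation by arm. Add one supplementary analysis of the primary endpoint in which any start or increase before the month-3 Holter counts as not arrhythmia-free. If the analysis plan already contains this, only the first item remains.

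**Cost:** one field in the randomisation system, one model term and one supplementary table. The article does not say that the reason for each start is captured, so the rule should not depend on it. In consequence, starts prompted by the qualifying arrhythmia soon after randomisation, or for an unrelated reason, will also count as failures and may lower the rate in both arms. For that reason the analysis should be supplementary only. No change to who receives a β-blocker is proposed.
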